## Abstract

**Design:**

The CapRI study is an open, controlled, prospective, randomised multi-centre phase III trial. Patients in study arm A will be treated as outpatients with 5-Fluorouracil; Cisplatin and 3 million units Interferon alpha-2b for 5 1/2 weeks combined with external beam radiation. After chemo-radiation the patients receive continuous 5-FU infusions for two more cycles. Patients in study arm B will be treated as outpatients with intravenous bolus injections of folinic acid, followed by intravenous bolus injections of 5-FU given on 5 consecutive days every 28 days for 6 cycles. A total of 110 patients with specimen-proven R0 or R1 resected pancreatic adenocarcinoma will be enrolled. An interim analysis for patient safety reasons will be done one year after start of recruitment. Evaluation of the primary endpoint will be performed two years after the last patients' enrolment.

**Discussion:**

The aim of this study is to evaluate the overall survival period attained by chemo-radiotherapy including interferon alpha 2b administration with adjuvant chemotherapy. The influence of interferon alpha on the effectiveness of the patients' chemoradiation regimen, the toxicity, the disease-free interval and the quality of life are analysed. Different factors are tested in terms of their potential role as predictive markers.

## Background

Only 10–20% of patients with pancreatic cancer can be resected with curative intent at the time of diagnosis. Loco-regional recurrence and/or metastatic disease develop in the majority of patients who undergo pancreatic resection. Relapse occurs within 9–15 months after initial presentation and patients have median life expectancies of only 12–15 months without adjuvant therapy. The 5-year survival rate of patients with resected pancreatic adenocarinoma is approximately 20% [1]. The statistics for the 80 to 90 % of patients who present with locally advanced and metastatic pancreatic cancer are even more dismal. Rarely do such patients achieve a complete response to treatment; median survival is 5–10 months and 5-year survival is near zero [2].

There is very little randomised data on adjuvant therapy for pancreatic carcinoma. The ESPAC-1 trial assessed the role of adjuvant therapy in a randomized study. 548 patients were enrolled in Europe in this first large randomized trial. There was evidence that adjuvant chemotherapy brought survival benefits. The five-year survival rate was 21 percent among patients who received chemotherapy [3].

In 1995 a phase II trial was initiated by the Virginia Mason Clinic, Seattle, USA combining pancreaticoduodenectomy and adjuvant therapy with 5-FU, cisplatin, interferon alpha and radiation therapy. Picozzi et al. reported treatment and results in a series of 43 patients with high-risk resected pancreatic adenocarcinoma (84% node positive, 19% margin positive). After a median follow-up period of 32 months the 2-year survival rate was 64% and the 5-year survival rate was 55% [4]. The overall recurrence rate was 12% of which 80% occurred within 2 years after surgery [5].

Since the Virginia Mason group reported such encouraging results in improving survival periods, there has been considerable interest in gaining increased experience with this therapy combination in an effort to confirm results and evaluate the toxicity profile of a modified version of this regimen.

Radio-sensitising properties of 5-FU (5-fluorouracil) and cisplatin are well known. The incorporation of interferon alpha-2b into a combined modality treatment program seems to offer a number of theoretical advantages. These include: 1) the radio-sensitisation effects of interferon alpha-2b and 5-FU perhaps synergistically [6]; 2) enhanced 5-FU based bio-availability; 3) a synergistic inhibition of pyrimidine metabolism with 5-FU; and 4) an independent immunomodulatory effect of interferon alpha-2b [7]. 5-FU and interferon alpha-2b have been used together to advantage in several cancer settings, but not as part of a combined modality program [8]. Cisplatin also has a radio-sensitising effect and shares similar properties of cytotoxic synergy with interferon alpha-2b and 5-FU in both experimental and clinical cancer systems [9]. In a previous study we were able to demonstrate in vitro that interferon alpha has direct inhibitory properties and that it reduces the enhanced proliferation rate and VEGF secretion after a single treatment with cisplatin [10]. The use of interferon alpha-2b, 5-FU and cisplatin together thus might represent a kind of "combination radiosensitizer" analogous to combination chemotherapy potentially useful in the treatment of pancreaticobiliary cancers, especially from the standpoint of local control.

## Design

### Trial organization

CapRI has been designed by the Department of Surgery, University of Heidelberg. The trial is carried out by the National Centre for Tumourdiseases (NCT). The NCT is a multidisciplinary clinical and basic research group as well as comprehensive cancer centre of the Medical School of the University of Heidelberg that has been founded to improve care and research for cancer patients. The trial is sponsored by the Manfred-Lautenschläger-Foundation. The sponsor is not involved in the database management and has no access to the randomisation code.

### Coordination

The trial is co-ordinated by the Surgical Department in cooperation with the National Centre for Tumourdiseases (NCT) at the University of Heidelberg. The Dept. of Surgery is responsible for overall trial management, trial registration (International Standard Randomised Controlled Trial Number (ISRCTN 62866759), ), database management, quality assurance including monitoring, reporting and for the scientific program of all trial related meetings.

### Investigators

Patients will be recruited by the Department of Surgery at the University of Heidelberg. Due to the multi-modal nature of the trial, all investigators are experienced oncologists from the fields of hematology/oncology, radiation oncology and general surgery at the University of Heidelberg co-operating in this trial.

### Adverse events committee

This committee consists of 3 independent physicians (medical oncologist, radiation oncologist and surgeon) and decides on the final diagnostic classification of critical clinical events. For all serious adverse events the documentation and relevant patient data are verified by the co-ordinating personnel before submitting the data to the Adverse Events Committee for diagnostic classification.

Analysis of safety related data is performed with respect to frequency of:

• Serious Adverse Events and Adverse Events stratified by body-system

• Adverse Events stratified by severity

• Adverse Events stratified by causality.

Patient toxicities will be assessed using the NCI Common Toxicity Criteria (CTC). Toxicity will be evaluated pretreatment, weekly during chemoradiation/ chemotherapy, prior to each course of infusional 5-FU and at follow-up. Unacceptable toxicity is defined as unpredictable, or irreversible Grade 4 toxicity. Decisions regarding weekly chemoradiation treatment and chemotherapy dose-adjustment will be made using the guidelines below and based on hematological parameters (ANC and platelets) monitored weekly during chemoradiation before each dose of cisplatin.

### Medication supply

All chemotherapeutic and immunotherapeutic agents are prepared and provided by the pharmacy of the University Hospital Heidelberg. Medication will be prepared for each patient specifically and delivered just prior to administration to the NCT.

### On-site monitoring

During recruitment of patients monitoring on site is performed according to good clinical practice (GCP) guidelines. The monitoring for this trial will be performed by a monitor from a Clinical Research Organisation (CRO) who is not involved in the trial or in completion of the case report form (CRF). The data management will be performed by an independent medical documentalist from the Institute for Medical Bioinformatics, University of Heidelberg. The medical monitoring will be done by two independent oncologists not involved in conducting this trial.

### Ethics, informed consent and safety

The final protocol was approved by the ethics committee of the University of Heidelberg, Medical School (L-042/2003). This study complies with the Helsinki Declaration in its recent German version, the Medical Association's professional code of conduct, the principles of Good Clinical Practice (GCP) guidelines and the Federal Data Protection Act. The trial will also be carried out in keeping with local legal and regulatory requirements. The medical secrecy and the Federal Data Protection Act will be followed.

Written informed consent is obtained from each patient in oral and written form before inclusion in the trial and the nature, scope, and possible consequences of the trial have been explained by a physician. The investigator will not undertake any measures specifically required only for the clinical trial until valid consent has been obtained.

### Patient selection

CapRI focuses on hospitalised patients over 18 years of age treated with pancreatic head resection for pancreatic adenocarcinoma during an 18-month period started in August 2004. Men and women over eighteen years of age with biopsy-proven completely resected (R0 or R1) pancreatic adenocarcinoma of the pancreatic head or uncinate process will be screened for participation in the study. A detailed overview of all eligibility criteria is given in Table 2.

### Study design

The CapRI study is designed as an open, controlled, prospective, randomised potentially multi-centre trial meant to evaluate the post-operative overall survival of patients with pancreatic adenocarcinoma receiving chemo-radiotherapy including interferon alpha 2b administration compared with adjuvant chemotherapy. The treatment is offered to a heterogeneous group of people under clinical circumstances, covering a wide age range, for both sexes and with heterogeneous characteristics / co-morbidities.

One year after inclusion of the first patient an interim analysis will be performed. If at this time point there is already a significant difference between both groups favouring the Virginia Mason scheme (p < 0.001) group B (5-FU/Folinic acid) will be stopped and replaced by group C (chemoradiation without interferon alpha). This group will help to define the possibly deciding influence of interferon alpha on the effectiveness of the Virginia Mason treatment protocol. Addition of group C to the study would be the matter of a separate study amendment. The study design will not be changed prior to agreement of the ethics committee.

### Study objectives

The primary objective is to compare the overall survival at two years postoperatively between two different methods of adjuvant treatment: therapy with 5-FU, cisplatin, interferon alpha 2b combined with radiation and the standard treatment from the ESPAC-1-Trial with 5-FU plus folinic acid.

Secondary objectives are to determine the role and the mechanism of interferon alpha 2b in patient's chemoradiation regimen, the toxicity, the disease-free interval and the quality of life. Different factors are tested in terms of their potential role as predictive markers.

### Randomisation and standardised treatment scheme

A block-randomisation-list is generated via computer system (SAS Version 8.2, SAS Institute Inc., Cary, USA). The sealed randomisation list is stored in the investigator file. Patients are randomised using sealed opaque envelopes in the independent study centre at the Department of Surgery (Clinical Study Centre – "Klinisches Studienzentrum Chirurgie" – KSC) until informed consent is attained and diagnostic procedures rule out any contra-indication for participation in this trial.

After randomisation and pre-treatment evaluation treatment must begin within 12 weeks of surgery. A port catheter will be placed after informed consent and randomisation will be done within one to two weeks after pancreatoduodenectomy for patients in study arm A. These patients will be treated with 200 mg/m^2^/day 5-FU by continuous intravenous infusion at days 1–38.

Cisplatin – 30 mg/m^2 ^(maximum single cisplatin dose of 60 mg) iv over 60 minutes on days 1, 8, 15, 22, 29, 36 (6 doses). Two to three hours before and after cisplatin administration the patients will receive hydration of at least 2 litres.

Interferon alpha-2b (Intron A) will be administered at a dose of 3 million units subcutaneously three times weekly (Monday, Wednesday, and Friday) for 17 doses. Non-steroidal anti-inflammatory drugs and steroids should be avoided if possible during Intron A treatment.

External beam radiation is to be given concurrently with chemotherapy with a total dose of 50.4 Gy in 28 fractions over 5.5 weeks (1.8 Gy/day). The pancreatic bed (i. e. resection margin) will be covered with a minimum margin of 2 cm. The hepatoduodenal ligament, origins of the celiac axis and superior mesenteric artery will be included. The AP/PA fields must include the entire duodenal C-loop as seen on the pre-operative CT scan. All patients will receive XRT per informed consent. A four-field technique with AP/PA and lateral fields and customised blocking is required. The beams will be weighted more heavily in the AP/PA fields (usually 2:1 compared to the lateral fields). The dose contribution from the lateral fields should be restricted to 20 Gy. Simulation should be done with the patient in the supine position with "arms up" position. A dosage greater than or equal to 10 MV photons should be used.

In study arm A the patients receive post-chemoradiation 5-FU infusions of 200/mg/m^2 ^/day by continuous intravenous infusion on days 64–101 and 120–161. The timing of these courses of infusional 5-FU will be adjusted in patients who have treatment interruptions.

Patients in study arm B will be treated with 20 mg/m^2 ^intravenous bolus injection of Folinic acid, D-L form, followed by 425 mg/m^2^/day intravenous bolus injection of 5-FU given on 5 consecutive days every 28 days for 6 cycles, i.e. 24 weeks.

The treatment protocol is outlined in figure 1.

### Investigation schedule and follow-up

Pre-treatment evaluation for patients who are enrolled in study arm A includes a single low-dose (3 Mio U) injection of INTRON A prior to therapy (LDI). Blood will be drawn for intensive immunological studies. All patients (study arm A or B) must have appropriate lab and radiographic studies (CXR; CT abdomen [done post-operatively]; CBC; platelet count; BUN; creatinine; bilirubin, CA 19-9, and CEA) conducted prior to study enrolment to meet eligibility criteria.

During days 1–38 [study arm A] or during chemotherapy [study arm B] patients will be assessed with laboratory evaluation: complete blood count and blood chemistries weekly. Laboratory parameters in study arm A will be evaluated before each dose of cisplatin. Creatinine will be determined also one day after administration of cisplatin. Blood from members of study arm A will be investigated weekly for immunological markers.

Vital signs (blood pressure and pulse rate) and temperature are controlled daily during treatment. Patients are evaluated prior to receiving chemoradiation or chemotherapy. Patients enrolled in study arm A are evaluated weekly by the medical oncology and radiation oncology team during treatment. The team will check patients at each visit for symptoms due to therapy; a physical examination and complete safety labs should be performed. The patients' mental state will be investigated weekly. The questionnaire CES-D will be used as support. The three module questionnaire will be filled out during weeks 3 and 6 (study arm A) or week 3 and week 24 for study arm B.

During post-chemoradiation, infusional 5-FU (Study Arm A) patients will be evaluated by a physician prior to treatment and every 2 to 3 weeks with clinical assessment and laboratory parameters including a CBC, electrolytes, BUN, and creatinine. If patients undergo post chemoradiotherapy infusional 5-FU coordinated by an outside medical oncologist, a study nurse will contact the patient at least once weekly by telephone.

In the post-treatment period patients will be seen every 3 months by the surgical service for the first 2 years, every 4 months for the third year, and every 6 months during the 4th and 5th post-treatment years.

The aggregate clinical, laboratory, and imaging evaluations required per protocol as well as the timing of the optional three module questionnaire are outlined in table 1.

The follow-up will be continued for two years. Follow-up data of overall survival will be evaluated annually.

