### Evaluation of the role of interferon alpha

In addition to the Virginia Mason and the MD Anderson study, an investigation of the effects and mechanism of INTRON A will be performed. IFN alpha seems to have the greatest activity of all interferons in malignancies [21-23] but its mode of action is poorly understood.

It probably consists of a combination of stimulation of cell-mediated cytotoxicity [24,25], direct antiproliferative anti-tumour activity, and an anti-angiogenic effect [15,26-31]. The known molecular and cellular effects of IFN-alpha appear to complement the mechanism of action of other therapies [28].

In view of the significant improvement in survival rates achieved by using interferon alpha in the Virginia Mason study, studies are now needed to define the molecular and immunologic mechanism(s) of this modality. If the mechanism of action of IFN-alpha is more clearly understood it can be applied more selectively and its therapeutic index will be enhanced.

Patients in study arm A at the CapRI trial will receive a single low-dose injection of 1 million units (LDI) prior to therapy. Accompanying immunological analysis should help to define predictive response markers. During therapy patients blood samples of approx. 20 ml will be drawn once a week for immunological studies. The panel will include immunophenotypings, detection of cytokine mRNA in lymphocytes, determination of cytokine patterns in peripheral blood, cellular cytotoxicity assays against autologous tumor cells and determination of apoptotic effects of interferon against autologous tumor cells.

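### The single pre-treatment interferon injection (LDI) in arm A is given as 3 million units in one section and 1 million units in another, so the article does not define its dose

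*Protocol article*

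**What the plan says.** The protocol article states the dose of the pre-treatment interferon injection twice, both times in current running text.

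- Investigation schedule and follow-up: the pre-treatment evaluation in arm A "includes a single low-dose (3 Mio U) injection of INTRON A prior to therapy (LDI". Blood is then taken for immunological studies.
- Evaluation of the role of interferon alpha: "Patients in study arm A at the CapRI trial will receive a single low-dose injection of 1 million units (LDI) prior to therapy". The next sentence gives the purpose: "Accompanying immunological analysis should help to define predictive response markers".

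Three other statements bear on the point.

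- Randomisation and standardised treatment scheme sets the on-treatment regimen separately: "Interferon alpha-2b (Intron A) will be administered at a dose of 3 million units subcutaneously three times weekly", for 17 doses.
- Evaluation of the role of interferon alpha also plans sampling that does not rely on the LDI: "During therapy patients blood samples of approx. 20 ml will be drawn once a week for immunological studies".
- Medication supply names one source for the drug: "All chemotherapeutic and immunotherapeutic agents are prepared and provided by the pharmacy of the University Hospital Heidelberg".

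Study objectives lists the role and mechanism of interferon, and the testing of possible predictive markers, among the secondary objectives.

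**The concern.** Whoever orders the LDI from this article has two figures for the same injection, and following either one departs from the other. That matters first because it is a drug dose given to patients, in every patient of one arm.

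It matters second for the marker work. The immune response after the LDI is meant to help find markers that predict response to treatment. That reading assumes that patients received the same stimulus. If some received one dose and some the other, a difference in immune response could reflect the dose or the patient, and the two could not be separated unless the dose given was on record. Even with uniform dosing, a reader of the article could not tell which dose a reported LDI result refers to.

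Patient selection says that the 18-month recruitment period started in August 2004. Some patients may therefore already have had the injection, and correcting the text alone would not establish what they received.

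**Working it through.** The article offers no figure to reproduce here. The check sets the two statements side by side and asks whether they can describe different things.

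| Feature | Investigation schedule and follow-up | Evaluation of the role of interferon alpha |
|---|---|---|
| Label | LDI | LDI |
| Arm | A | A |
| Timing | before therapy | before therapy |
| Number of injections | one | one |
| Purpose | immunological studies | immunological analysis for predictive markers |
| Dose | 3 million units | 1 million units |

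Every feature except the dose agrees, so the two entries describe one procedure.

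**Size of the conflict.** 3 million / 1 million = 3, a threefold difference.

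**Patients concerned.** Statistical considerations and sample size estimation plans 110 randomised patients. The randomisation section describes a block list but gives no allocation ratio. Assuming 1:1, 110 / 2 = 55 patients in arm A.

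**Does anything else in the article resolve it?**

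- The on-treatment dose of 3 million units is a separate item, with its own route, schedule and number of doses. That the same figure appears there does not establish the LDI dose.
- The description as low-dose is attached to both figures, so it does not discriminate between them.
- Neither statement is superseded text from an amendment log.
- The contents of Table 1 (investigation schedule) and Figure 1 are not in the text at hand. Whatever they show, the two prose statements would still disagree.

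**What depends on the LDI dose?**

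- The response measured after the LDI, and any predictive marker built on it: yes, if dosing was mixed.
- The weekly immunological samples during therapy: these are taken under the separately stated treatment regimen, and the article does not tie them to the LDI dose.
- The primary endpoint and its analysis (overall survival, Kaplan-Meier and Cox regression): no.
- The sample size (96, raised to 110) and the 80% power: no. These rest on the two-year survival rates of 35% and 60%, the accrual and follow-up times and the allowance for non-completers.

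**The case against.** The strongest reply is that the article shows a conflict in its own text and nothing about what was done. It condenses a full protocol approved by the ethics committee, and that protocol and the pharmacy order may state one dose consistently. A single hospital pharmacy prepares all agents for each patient individually. The Investigators section names one recruiting department, and Study design calls the trial only potentially multi-centre, although the Abstract calls it multi-centre. Uniform dosing is therefore plausible.

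This stands as a limit on the consequence. Mixed dosing is a possibility to be checked, and the article does not show that it occurred. It does not remove the contradiction: the article did not leave the dose to another document but stated it twice, differently.

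Two stronger readings are tempting and are not supported.

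- A reader might infer that the conflict makes the trial's marker data unreadable. It touches only the response to one injection. The weekly on-therapy samples do not depend on it, and the LDI data themselves remain interpretable if one dose was used throughout or if the dose each patient received is known.
- A reader might infer from the description as low-dose, set against the on-treatment dose, that one of the two figures must be the error. Since both figures carry that description, the article does not support the inference.

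Nor does the article support a claim of harm: neither LDI figure exceeds the amount per injection that it plans during treatment.

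**Conclusion.** The point holds as an internal contradiction. One pre-treatment injection in arm A carries two doses that differ by a factor of three, and the article contains nothing that decides between them. As written, the LDI dose is undefined for all arm A patients; the figure of about 55 rests on an assumed 1:1 allocation.

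The need to correct it rests on its being a dose given to patients. The statistical consequence is narrower and conditional: confounding of response with dose in the LDI-based marker analysis, a secondary objective, and only if more than one dose was in fact given. The trial's main comparison is untouched.

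**What to change.** 1. Reconcile Investigation schedule and follow-up with Evaluation of the role of interferon alpha, using the approved full protocol and the pharmacy order, and correct whichever statement is inconsistent with them. This review does not say which dose is right.
2. Confirm and record the LDI dose actually given to each arm A patient, including those already treated.
3. If the records show one dose throughout, state that dose with the LDI results; the analysis needs no other change. Only if they show more than one dose, analyse the LDI markers by dose received and do not pool across doses.

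The cost is one corrected line and a check of pharmacy records and case report forms. If doses turn out to have differed, one further variable enters the marker analysis, and the patients available at each dose will be fewer than the arm as a whole.

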### Assessment of quality of life

Measurement of quality of life is one of the secondary objectives of the trial. Overall survival, return to previous employment as well as persistence of symptoms, the ability to perform appropriate activities and to care for oneself are criteria applied in the three questionnaires used in this study.

EORTC QLQ-C30 is a general measure of qualitiy of life in cancer patients. It incorporates nine multi-item scales: five functional scales (physical, role, cognitive, emotional, and social); three symptom scales (fatigue, pain, and nausea and vomiting); and a global health and quality-of-life scale [17]. Specific symptoms (dyspnoea, insomnia, anorexia, constipation, diarrhoea, and financial impact) are measured as six single items. This instrument has been used extensively with a variety of cancer patients and was able to discriminate between individuals with metastatic and non-metastatic disease, as well as between patients at different stages of illness. The scale has good internal consistency (alpha > 0.70), and good test re-test reliability (0.80 to 0.90) [18].

To assess disease-specific symptoms for patients with pancreatic cancer the pancreatic specific module (QLQ-PAN26) [19] that has been designed to use long with the general measure is used in this study.

The CES-D [20] is a 20-item self-report measure of depression that emphasises the emotional dimension. Its emphasis on the affective components of depression and is preferable for use in medical populations. It has demonstrated high internal consistency in both the general population and in patient populations and convergent validity with other measures of depression [21].

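### Quality-of-life forms are set at weeks 3 and 6 in arm A but weeks 3 and 24 in arm B, so the second stated on-treatment assessment confounds arm with time and treatment phase

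*Protocol article*

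**What the plan says.** The section on assessment of quality of life states: "Measurement of quality of life is one of the secondary objectives of the trial". The instruments are the QLQ-C30, the QLQ-PAN26 and the CES-D. Investigation schedule and follow-up says, without qualification, that the three-module questionnaire will be "filled out during weeks 3 and 6 (study arm A) or week 3 and week 24 for study arm B". No reason is given for the different weeks. The same section later refers the reader elsewhere for the visit schedule, "as well as the timing of the optional three module questionnaire are outlined in table 1". Table 1 itself is not in the text available; the closing Note gives only its title.

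The treatment calendars are in Randomisation and standardised treatment scheme. Arm A receives "5-FU by continuous intravenous infusion at days 1–38" with concurrent cisplatin, interferon and radiation, and then further 5-FU "by continuous intravenous infusion on days 64–101 and 120–161". Arm B receives folinic acid and bolus 5-FU "given on 5 consecutive days every 28 days for 6 cycles, i.e. 24 weeks".

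**The concern.** A between-arm comparison of patient-reported outcomes needs both arms measured at the same elapsed time, or at treatment phases chosen deliberately as equivalent. The stated schedule does neither for the second form. If the second form is compared between arms, a difference could come from the regimen, from the 18 weeks of further recovery or disease course in arm B, from being measured at the end of a course rather than well after one, or from the loss of patients who died in between. These sources cannot be separated afterwards, because data not collected at a common week cannot be recovered by analysis.

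This matters because the trial is open-label and, under Statistical considerations, sets no stopping rule on the overall number of toxicities, on the ground that high rates of reversible toxicity may be acceptable for a large survival gain. Patient-reported burden is therefore part of what a reader will weigh against survival.

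**Working it through.** **Inputs.** Questionnaire weeks: Investigation schedule and follow-up. Dosing days: Randomisation and standardised treatment scheme. Survival assumptions: Statistical considerations and sample size estimation.

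**Assumptions.** Week w covers days 7(w−1)+1 to 7w from treatment start, and treatment runs without delay.

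**1. The plan's own figure.** Arm B: 6 cycles × 28 days ÷ 7 = 24 weeks, which reproduces the stated duration. Counting weeks from treatment start therefore fits the document.

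**2. Dosing calendars.**
- Arm A: chemoradiation on days 1–38 (cisplatin on days 1, 8, 15, 22, 29 and 36); 5-FU on days 64–101 and 120–161.
- Arm B: days 28c+1 to 28c+5 for c = 0 to 5, that is days 1–5, 29–33, 57–61, 85–89, 113–117 and 141–145.

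**3. Where the stated forms fall.**

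| Form | Days | Days on treatment | Days since last dose |
|---|---|---|---|
| Arm A, week 3 | 15–21 | 7 of 7 | 0 |
| Arm A, week 6 | 36–42 | 3 of 7 (days 36–38) | 0, then 1–4 |
| Arm B, week 3 | 15–21 | 0 of 7 | 10–16 (from day 5) |
| Arm B, week 24 | 162–168 | 0 of 7 | 17–23 (from day 145) |

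The second forms are 24 − 6 = 18 weeks apart.

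**4. Sensitivity to the meaning of week.** If week w means after w completed weeks, week 3 is days 22–28, week 6 is days 43–49 and week 24 is days 169–175. Arm A is still on chemoradiation at week 3 but has finished it by week 6. Arm B is off drug at both of its times. The 18-week gap is unchanged.

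**5. Survivor selection on the planning assumptions.** Hazard = −ln(two-year survival)/24:
- arm B: −ln(0.35)/24 = 0.0437 per month (stated as 0.044);
- arm A: −ln(0.60)/24 = 0.0213 per month (stated as 0.021).

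With 30.44 days per month, week 6 is 42/30.44 = 1.38 months and week 24 is 168/30.44 = 5.52 months. Proportion dead = 1 − exp(−hazard × months):

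| Time | Arm A | Arm B |
|---|---|---|
| Week 6 | 3% | 6% |
| Week 24 | 11% | 21% |

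The stated schedule sets arm A at 3% against arm B at 21%, a gap of 18 points. At a common week the gap is 3 points (week 6) or 10 points (week 24). The excess comes from timing; the remainder is the assumed treatment effect.

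**6. Common weeks, if adopted.** At week 6, arm A is at the end of chemoradiation and arm B is 3–9 days after its cycle 2 doses (last on day 33). At week 24, arm A is 1–7 days after day 161 and arm B is 17–23 days after day 145, so both have passed their last planned dose.

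**The case against.** The strongest objection is that Table 1 is said to give the questionnaire timing and is not shown. A reader might infer from the text that arm A has no form during its later 5-FU courses or afterwards, and that the quality-of-life objective cannot be answered. The document does not support either. Table 1 may hold baseline, later or follow-up forms, and week 3 is shared. This part stands, and it limits the point to the on-treatment weeks that the text states. Further forms would allow other comparisons but would not align those weeks.

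Nor does any section say that the week 6 form will be set against the week 24 form, and the choice of visits to compare may be left to an analysis plan. That is fair, but the analysis plan can only choose among weeks that were collected.

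Three other readings go too far. First, that arm A is measured during chemoradiation both times: this is exact for week 3, but only 3 of 7 days of week 6 qualify, and none do if completed weeks are meant. Second, that the bias has a known direction or size: whether arm B's symptoms have cleared 10–16 days after dosing is not stated, and no quality-of-life means, standard deviations or analysis method are given. Third, that 21% against 3% dead measures the distortion: it mixes timing with the assumed survival benefit, and about 21% against 11% would remain at a common week 24.

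Finally, the CES-D also supports a weekly mental-state check, so the problem concerns mainly the QLQ-C30 and QLQ-PAN26.

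**Conclusion.** The point holds for the on-treatment times stated in the text. The second questionnaire is 18 weeks apart between arms and falls in different treatment phases, so arm is confounded with time since treatment start, with phase and, in part, with survivor selection. The one shared week compares arm A on chemoradiation with arm B in the rest part of its cycle. These statements assume that weeks count from treatment start and that treatment is not delayed; the 18-week gap does not depend on how the week is numbered. The death proportions also assume the plan's constant hazards. The amount of bias in any quality-of-life score cannot be computed from the document.

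Severity is moderate. A secondary objective is affected; the primary survival comparison, the sample size and the safety monitoring are not.

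**What to change.** - Collect the questionnaire at weeks 3, 6 and 24 in both arms, and state that weeks count from the start of treatment. Randomisation is not a safe origin: it is planned one to two weeks after surgery (as stated for arm A), while treatment may start as late as 12 weeks after surgery, so forms at weeks 3 and 6 from randomisation could precede any treatment.
- Base between-arm quality-of-life comparisons during treatment on these common weeks only.
- State that week 3 falls in arm B's rest period, so that the result is read accordingly.
- Remove the word optional, so that the reference to Table 1 agrees with the plain statement that the form is completed and with its role in a secondary objective. Make Table 1 match.

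The cost is one extra self-report form per patient (week 24 in arm A, week 6 in arm B) and an edit to the schedule. Treatment is unchanged. Common weeks remove the part of the survivor imbalance that comes from timing, but not the part that comes from a real survival difference.
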